### Exploratory trial

#### Study design

An exploratory two-arm pilot RCT will be undertaken to evaluate the intervention. Participants will be randomized to receive either the habit-based booklet (intervention condition), or an existing UK National Health Service (NHS) fact sheet on physical activity and sedentary behaviour in older adulthood (control condition). Assessments will be made at baseline, and 8 and 12-weeks post-baseline (follow-up). Participants will be blinded to condition, but owing to staffing constraints, the researcher administering the intervention will be required to obtain outcome measures, so will be unblinded. Primary outcome measures will be recruitment and attrition rates, and secondary outcome measures will be changes in behaviour, habit, health and wellbeing. The study was registered on the International Standard RCT Number (ISRCTN) Register^a^ (ISRCTN47901994) in January 2014. The trial start date differs from that stated on the ISRCTN Register (April 2014) because of multiple unforeseen delays. The new planned start date is September 2014, and the trial is scheduled to end in February 2015. Recruitment had not begun at the time of submission of this manuscript.

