#### Study setting

Participants (*n* = 120) will be identified through general practices in Barnet and Enfield, boroughs in north London, UK, chosen because of the high percentage of older adults (≈15%). The sample size has been pragmatically determined, to obtain sufficient data to capture variability and inform a power calculation for a larger-scale definitive RCT, while minimizing trial costs [49]. Consent will be obtained at the general practice, and data collection and treatment administration undertaken in participants’ homes.

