### Randomization

Participants will be block randomized to study conditions, using a 1:1 allocation ratio, according to a random number list, computer-generated using specialist software by an independent trial administrator. Randomization will occur between the consent session and the first (baseline) home visit. After completing the consent session, the researcher will phone the trial administrator, who will consult the random number list to allocate the participant to a condition. A unique identification code denoting the participant and the participant’s general practice will be allocated by the trial administrator, to permit matching of data across time points.

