#### Analysis of secondary outcomes

Analyses of changes in secondary outcomes (physical activity, habit, wellbeing, physical health, functioning) will be run using valid data at all three time points to analyze changes among completers only. Non-completers will be accounted for by using last-observation-carried-forward and baseline-observation-carried-forward analyses, the latter to ensure a more conservative assessment of potential changes in outcomes. Between-group changes in outcomes over the first 8 weeks will be assessed using *t* tests, and within-group changes examined using repeated measures analysis of variance (ANOVA). To evaluate whether habit change is associated with behaviour change, we will calculate correlations between changes in automaticity for generic physical activity and sedentary behaviour (and, in the intervention group, for each target habit), and changes in physical activity within each group. Effect sizes for changes in self-reported physical activity will be used to inform a power calculation to determine the sample size required for a definitive RCT. Qualitative interview data will be analyzed using thematic analysis.

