## Discussion

Older adults tend to spend too much time sitting and do too little physical activity [6]. Our study will assess the feasibility of evaluating an intervention for older adults that seeks to displace periods of prolonged sedentary behaviour with physical activity. Our intervention represents a ‘small changes’ approach, recommending forms of physical activity that can be performed at low intensity, and it uses principles of habit formation to promote the automatization and integration of these actions into everyday routines [37]. The intervention has been iteratively developed using empirical evidence of older adults’ activity preferences, verified as appropriate by a panel of experts. The intervention is theory-based, and the activities recommended in the tips are evidence-based, in that they have been shown to improve health and functioning outcomes. The RCT will compare our intervention booklet with a fact sheet that is readily available to older adults and that recommends physical activity and minimizing sedentary behaviour, but offers few suggestions of how this might be achieved. This exploratory RCT aims to test study procedures ahead of a future, fully-powered definitive RCT, but the collection of data on behaviour, habit, health, wellbeing at baseline and two follow-up points permits analysis of changes in these indices.

We acknowledge the limitations of our study design. Selection bias may impact findings. Enrolment into the study requires that patients return a declaration of interest by regular post, and attend their general practice to be consented. Older adults who leave the house more often tend to accrue more physical activity [54], and so these procedures favour those at the more active end of the inactivity spectrum, rather than the highly inactive and sedentary older adults who might benefit most from intervention. Taking consent at the practice was judged necessary to garner interest among practices, which receive financial incentives for consenting on the premises. We have attempted to minimize participant burden by conducting all post-recruitment procedures at participants’ homes, and offering shopping vouchers to recognise their efforts.

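### Arms are compared by t tests on change to 8 weeks; adjusting the 8-week value for its collected baseline would usually be more precise and would remove the effect of chance baseline imbalance

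*Protocol article*

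**What the plan says.** The protocol article's section on analysis of secondary outcomes covers physical activity, habit, wellbeing, physical health and functioning, each analysed as a change. For the arm comparison it states: "Between-group changes in outcomes over the first 8 weeks will be assessed using" t tests. The only other model it names for these outcomes is a repeated measures ANOVA, reserved for change within each group, so it does not adjust the arm comparison. No covariate for the baseline value appears anywhere in the article.

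The study design section and Table 1 schedule measurement at baseline, 8 weeks and 12 weeks. Table 1 marks all three for every behavioural, psychological and health measure that both arms complete. The Discussion relies on this: "the collection of data on behaviour, habit, health, wellbeing at baseline and two follow-up points permits analysis of changes in these indices".

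On size and allocation, the study setting section gives 120 participants and says: "The sample size has been pragmatically determined, to obtain sufficient data to capture variability and inform a power calculation for a larger-scale definitive RCT". The randomization section adds: "Participants will be block randomized to study conditions, using a 1:1 allocation ratio". The analysis section then says that effect sizes for change in self-reported physical activity will inform the power calculation for the definitive trial.

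**The concern.** A change score uses the baseline by subtracting it, which fixes the slope of follow-up on baseline at 1. ANCOVA estimates that slope from the data. If the true slope is not 1, the change-score comparison carries avoidable noise. It also retains a part of whatever baseline difference chance produces between the arms: with a slope below 1, the arm that started worse appears to improve more.

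Two things are at stake. Each secondary estimate may have a wider interval than the collected data allow. And the estimate for self-reported physical activity, with its SD, goes forward into the design of the next trial, so both the inefficiency and any imbalance artefact go with it.

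**Working it through.** The plan gives no SD, correlation, alpha or power for these outcomes, so there is no stated figure to reproduce. The check asks how the two analyses compare under stated assumptions.

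**Inputs from the article.** 120 participants at 1:1, so 60 per arm before attrition.

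**Assumptions.** Baseline SD = 1; follow-up SD = 1 at first, relaxed below; correlation r from 0.3 to 0.9; two-sided 5% level.

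**Precision.** With equal SDs:
- variance of a change score = 2(1 − r)
- residual variance under ANCOVA = 1 − r² = (1 − r)(1 + r)
- ratio, ANCOVA to change score = (1 + r)/2
- 95% CI half-width = 1.96 × SD × √(2/60)
- total N at which a change-score analysis matches ANCOVA with 120 = 120 / ratio, rounded up

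| r | variance ratio | half-width, change score (SD) | half-width, ANCOVA (SD) | change-score N matching ANCOVA with 120 |
|---|---|---|---|---|
| 0.3 | 0.65 | 0.423 | 0.341 | 185 |
| 0.5 | 0.75 | 0.358 | 0.310 | 160 |
| 0.7 | 0.85 | 0.277 | 0.256 | 142 |
| 0.9 | 0.95 | 0.160 | 0.156 | 127 |

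**Chance imbalance.** The baseline difference between arms has SE √(2/60) = 0.183 SD. The chance that it exceeds 0.25 SD in either direction is 2(1 − Φ(0.25/0.183)) = 0.17 per outcome. Given a baseline gap D, the change-score estimate is shifted by (slope − 1) × D, which is −(1 − r)D with equal SDs. For D = 0.25 SD the shift has size 0.175, 0.125, 0.075 and 0.025 SD at r = 0.3, 0.5, 0.7 and 0.9.

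**Simulation** (20,000 trials of 60 v 60, equal SDs):
- Variance ratios were 0.760 at r = 0.5 and 0.855 at r = 0.7, against 0.75 and 0.85 in theory.
- Among trials with a baseline gap near 0.2 SD, the mean shift was −0.093 and −0.055 SD for change scores (theory −0.10 and −0.06), and +0.007 and +0.005 SD for ANCOVA.
- The correlation of the estimate with the baseline gap was −0.50 and −0.39 for change scores, and 0.00 for ANCOVA.

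**Unequal SDs.** With follow-up SD k times the baseline SD, the slope is rk, the ANCOVA variance is k²(1 − r²) and the change-score variance is k² + 1 − 2rk. Take k = 1.5 for illustration:
- r = 0.5: slope 0.75; ratio = (2.25 × 0.75)/(3.25 − 1.5) = 1.6875/1.75 = 0.96
- r = 0.7: slope 1.05; ratio = (2.25 × 0.51)/(3.25 − 2.1) = 1.1475/1.15 = 0.998

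**Carry-over to the definitive trial.** For an assumed true difference of 0.3 SD at 80% power with equal SDs, the number per arm sized from the change-score SD against the residual SD is 245 v 159 (r = 0.3), 175 v 131 (0.5), 105 v 89 (0.7) and 35 v 34 (0.9).

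**The case against.** The strongest reply is that the planned test is not wrong. Under randomization a t test on change is unbiased and keeps its type I error. The shift described above is conditional on an observed imbalance, and over repeated randomization it is already counted in the standard error: at r = 0.5 the SE of the change-score difference is √(2 × 1/60) = 0.183 SD, so a 0.125 SD shift is about 0.7 SE. This stands. A reader might infer that the plan's estimates are biased or its tests invalid; the documents do not support that.

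Second, the size of the gain depends on figures the article does not give. At r = 0.9 it is 5%. The simple ratio needs equal SDs, and the entry criteria (low activity, long sitting) may narrow the baseline spread of the behavioural outcomes. With a follow-up SD 1.5 times the baseline SD, the gain at r = 0.5 falls from 25% to about 4%, and at r = 0.7 the change score slightly under-corrects. So it is also wrong to say that a change score over-corrects whenever r is below 1; what matters is the slope. The carried-forward analyses set follow-up equal to baseline for anyone lost before 8 weeks, which will generally raise r and shrink the gain further. All this stands and limits the claim, but it does not reverse it: apart from the negligible cost of estimating one slope, ANCOVA is not expected to do worse.

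Third, the stakes are limited. The primary outcomes are recruitment and attrition, the sample size was set pragmatically, and the Discussion concedes that effects will be hard to identify. That also stands. But the protocol does send one of these effect sizes into the next trial's power calculation, so the choice has a use beyond description.

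**Conclusion.** The point holds as a modest, nearly free improvement to a valid analysis. The t tests on change are generally less precise than ANCOVA and leave part of any chance imbalance in the estimate whenever the slope is not 1. With equal SDs, the variance saving is 35% to 5% as r runs from 0.3 to 0.9, and a 0.25 SD baseline gap moves the change-score estimate by 0.175 to 0.025 SD. These figures assume r, assume equal SDs, and take 60 per arm with no loss; fewer completers would make chance imbalance larger.

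Three limits apply. The point concerns only outcomes that a t test can compare between arms, not recruitment, attrition, the tick sheet, the habit items given to the intervention group alone, or the exit interview. A reader might also take the absence of stratification on baseline activity as a defect, but a condensed article's silence on it is no finding, and stratification would not balance this many outcomes anyway. Finally, randomization precedes the baseline home visit, where an unblinded researcher takes the objective measures before treatment. Those values remain usable as covariates, and the caveat applies equally to change scores.

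**What to change.** In the section on analysis of secondary outcomes, replace the between-group t tests with ANCOVA: the 8-week value regressed on arm and on the baseline value of the same outcome, reporting the adjusted mean difference with its 95% CI. Use the same model in the completer analysis and in both carried-forward analyses. For self-reported physical activity, report r and the residual SD after adjustment, and take the adjusted estimate and that residual SD into the definitive trial's power calculation.

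The cost is a sentence or two of analysis wording. No new data, visits or participants are needed, and the article states that the trial has not begun.

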## Abstract

**Background:**

Many older adults are both highly sedentary (that is, spend considerable amounts of time sitting) and physically inactive (that is, do little physical activity). This protocol describes an exploratory trial of a theory-based behaviour change intervention in the form of a booklet outlining simple activities (‘tips’) designed both to reduce sedentary behaviour and to increase physical activity in older adults. The intervention is based on the ‘habit formation’ model, which proposes that consistent repetition leads to behaviour becoming automatic, sustaining activity gains over time.

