### Aims and objectives

This protocol describes work to develop a theory- and evidence-based behaviour change intervention aiming to displace prolonged sitting time (sedentary behaviour) with at-least-light-intensity physical activity in older adults. The intervention seeks to promote the formation and integration of physical activity habits into existing normally sedentary routines. An exploratory randomized controlled trial (RCT) will compare the intervention with a control fact sheet setting out national guidelines for physical activity and sedentary behaviour. The primary objective of the RCT is to assess the feasibility of our intervention and our study procedures, as a basis for informing a large-scale future RCT. The secondary objective is to assess changes in behaviour, health and wellbeing. The intervention is being developed in line with the Medical Research Council complex interventions framework [32]. This protocol has been prepared in accordance with Standard Protocol Items: Recommendations for Interventional Trials (SPIRIT) and Template for Intervention Description and Replication (TIDieR) guidelines [33, 34], completed checklists for which are provided as additional files (see Additional files 1 and 2).

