#### Behaviour measures

Among the intervention group, adherence to each of the activities recommended in the booklet will be self-reported on ‘tick sheets’ for eight weeks post-baseline. Participants will be requested to return tick sheets to the research team either by post in prepaid envelopes or at the 8-week follow-up visit.

Generic physical activity and sedentary behaviour will be self-reported using a short form of the International Physical Activity Questionnaire [51] and a validated sedentary behaviour questionnaire [52], and objectively measured over three 7-day periods using activPAL3 accelerometers (PAL Technologies, Glasgow, Scotland). These devices are lightweight, do not provide physical activity feedback to wearers, and are sensitive to transitions between sitting, lying down (both sedentary behaviours) and standing (a physical activity), so can distinguish true sedentary behaviour from inactivity [63]. Data on total sitting time, physical activity (step count, cadence (speed) of steps), and sit-to-stand transitions during each wear period will be entered into analyses.

Devices will be pre-programmed to begin data collection on the day following their fitting, and participants’ unique identifier codes will be programmed into each unit to facilitate data matching. The activPAL device will be fitted to the participant’s thigh, with the same thigh used for all wear periods, using a waterproof dressing to allow showering and bathing as normal.

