#### Psychological measures

Habit strength for generic physical activity and sedentary behaviour and, in the intervention group only, each of the behaviours recommended in the tips will be assessed using a single automaticity item, adapted to each focal behaviour. This item (‘(Behaviour X) is something I do without thinking’) is derived from the automaticity subscale of the Self-Report Habit Index (SRHI) [64, 65]. A single item was chosen on the basis of data emerging from the preliminary field test that suggest that participants struggle to understand SRHI items, or show understandings that deviate from those intended by researchers. The chosen item has shown satisfactory content and predictive validity, and convergent validity with its parent index [64].

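### Change in sedentary habit is correlated only with change in physical activity, so the sitting half of the dual target goes unexamined; the outcome list also omits sedentary behaviour

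*Protocol article*

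**What the plan says.** All references are to the protocol article.

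- **Target.** Aims and objectives describes an intervention "aiming to displace prolonged sitting time (sedentary behaviour) with at-least-light-intensity physical activity in older adults". The Abstract gives a dual target: the booklet is "designed both to reduce sedentary behaviour and to increase physical activity in older adults".
- **Measures of behaviour.** Table 1 lists sitting under three instruments (accelerometry, the short activity questionnaire and the sedentary behaviour questionnaire), each at baseline, 8 weeks and 12 weeks. Behaviour measures opens its list of accelerometer variables for analysis with "Data on total sitting time". It names physical activity separately, as step count and cadence, and adds sit-to-stand transitions.
- **Measures of habit.** Psychological measures covers "Habit strength for generic physical activity and sedentary behaviour", with one automaticity item for each. Table 1 shows both at all three time points. The intervention group also rates ten tip-specific habits.
- **Analysis.** Analysis of secondary outcomes covers "changes in secondary outcomes (physical activity, habit, wellbeing, physical health, functioning", and the parenthesis closes there. The mechanism analysis begins "To evaluate whether habit change is associated with behaviour change, we will calculate correlations". Taken separately by arm, the variables to be paired are "changes in automaticity for generic physical activity and sedentary behaviour (and, in the intervention group, for each target habit), and changes in physical activity".

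**The concern.** The question put is whether habit change accompanies behaviour change. For a sedentary habit, the matching behaviour is sitting. The plan names a different one, physical activity, and no correlation between habit and sitting is stated anywhere in the article.

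This is not a detail left for a fuller document to supply. The article fixes a specific pairing, and for one of the two generic habits the pairing does not fit the question.

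If the section is followed as written, the trial cannot say whether a weaker sitting habit goes with less sitting. That matters for two reasons. The Intervention section expects the tips to disrupt sedentary habits. The Discussion makes a definitive trial depend partly on promise in changing sitting as well as activity.

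**Working it through.** The check is mainly textual. The sample size of 120 was set pragmatically, and the article states no power, effect size or correlation to reproduce.

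**1. Count the planned pairs.** Table 1 gives two generic habit items (both arms) and ten tip items (intervention arm only). For each activity measure and each change interval:

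- generic pairs: 2 habits × 2 arms = 4
- tip pairs: 10 × 1 arm = 10
- total: 4 + 10 = 14

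The generic sedentary item supplies one pair per arm, so 2 of the 14 are mismatched. The generic activity item is paired with its own behaviour. The tips are themselves activities, so pairing the tip habits with activity is reasonable.

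**2. Could physical activity be shorthand for both behaviours?** The sentence that defines the correlations names physical activity and sedentary behaviour as two things on the habit side, then uses only the first on the behaviour side. Table 1 lists them as separate constructs. Behaviour measures separates sitting time from activity. The shorthand reading does not fit.

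**3. Would the planned pairing pick up sitting anyway?** Suppose a participant replaces some sitting with standing still. Sitting time falls by that amount and standing time rises by the same amount. Stepping is unchanged, so step count and cadence need not move. The sedentary habit could weaken in step with sitting while the planned correlation stays flat.

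**4. Compare the two places that mention sitting.** Behaviour measures commits total sitting time to analyses without saying which. Analysis of secondary outcomes lists five domains, and sedentary behaviour is not among them. The two do not agree.

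**5. Illustration only.** Every correlation here is an assumption. Let the correlation between change in sedentary habit and change in sitting be 0.40, and let the absolute correlation between change in sitting and change in activity be 0.3 to 0.6. If the habit acts on activity only through sitting, the planned correlation is the product:

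- 0.40 × 0.3 = 0.12
- 0.40 × 0.6 = 0.24

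With 60 per arm (120 at 1:1, no attrition) and a two-sided 5% test, Fisher's z gives power ≈ Φ(atanh(r) × √(60 − 3) − 1.96), with √57 = 7.55:

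- r = 0.40: 0.424 × 7.55 = 3.20; Φ(1.24) = 0.89
- r = 0.24: 0.245 × 7.55 = 1.85; Φ(−0.11) = 0.46
- r = 0.12: 0.121 × 7.55 = 0.91; Φ(−1.05) = 0.15

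At the other extreme, if sitting and activity were perfectly inverse, the product would be 0.40 × 1 = 0.40 and nothing would be lost. The result therefore depends on an unknown correlation.

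**The case against.** The strongest reply has four parts.

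- **Sitting is not dropped.** Behaviour measures puts total sitting time first among the variables to be analysed. The Abstract and Study design define secondary outcomes broadly as changes in behaviour. A reader might infer from the list that sitting will go unanalysed; the documents do not support that. What stands against the plan is a list that disagrees with the measures section, and a correlation that the general commitment does not repair.
- **The authors treat the two behaviours as reciprocal.** The Endnote argues that less sitting must mean more activity because standing counts as activity, and the Discussion describes this analysis simply as relating habit to behaviour. This explains how the wording may have arisen. It does not close the gap, because the activity variables named for analysis are step count and cadence, which standing need not change.
- **Physical activity is also a target.** This stands in full. A reader might infer that the mechanism analysis misses the trial's target behaviour altogether. It does not: it covers the activity half and misses the sitting half.
- **The analysis is exploratory.** It is a secondary analysis in a feasibility trial whose primary outcomes are recruitment and attrition, and the Discussion says that it cannot settle causation. That limits the consequence, and it makes it speculative to say that a weak correlation would be taken as proof of no habit mechanism. It does not justify pairing a habit with a behaviour other than its own.

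**Conclusion.** The point holds in a limited form. As written, change in generic sedentary-behaviour automaticity is related only to change in physical activity, so the link between sitting habit and sitting is not examined. The outcome list omits sedentary behaviour, although Table 1 and Behaviour measures include it. The extent is one generic pairing in each arm and one incomplete list; the generic activity pairing needs no change, and the tip pairings are reasonable.

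A reader might take the drop from about 89% power to between 15% and 46% as the loss caused by the plan. The documents do not support that. The figures rest on assumed correlations, on an effect acting only through sitting, on full recruitment and retention, and on a significance test that the section does not state for these correlations. They show that a real link could be diluted, not by how much. The conclusion rests on the text alone. It is worth correcting because the correction is nearly free and, by the article's own account, recruitment had not begun.

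**What to change.** Amend Analysis of secondary outcomes as follows.

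1. Correlate change in sedentary-behaviour automaticity with change in activPAL total sitting time in each group, with self-reported sitting as support.
2. Keep physical-activity automaticity and the tip habits paired with change in physical activity. Pairing the tip habits with sitting as well is optional and should be labelled exploratory, since it adds ten correlations in one arm.
3. Add sedentary behaviour to the list of secondary outcomes, so that it agrees with Table 1 and Behaviour measures.

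**Cost.** The change is one of wording, and every variable is already scheduled. For each change interval, item 1 needs 2 correlations with activPAL sitting time (one per arm) and at most 4 supporting ones (two questionnaires × two arms). The only drawback is these few extra exploratory estimates, which should be reported as such.

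### The definitive trial's power calculation would rest on the pilot's observed effect in self-reported physical activity, which is too imprecise for the purpose and leaves out the activPAL sitting data

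*Protocol article*

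**What the plan says.** Two places in the protocol article describe how this trial will feed the sizing of the next one.

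- **Study setting** gives the reason for recruiting 120: "to obtain sufficient data to capture variability and inform a power calculation for a larger-scale definitive RCT".
- **Analysis of secondary outcomes** names the input: "Effect sizes for changes in self-reported physical activity will be used to inform a power calculation". No standard deviation, target difference, correlation or attrition rate is mentioned there.

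The intervention is described under **Aims and objectives** as "aiming to displace prolonged sitting time (sedentary behaviour) with at-least-light-intensity physical activity in older adults". Under **Behaviour measures**, activPAL3 devices are worn by all participants for three 7-day periods, and total sitting time is among the data to be analysed. Table 1 lists sedentary behaviour under three instruments at baseline, 8 weeks and 12 weeks.

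The list of analysed outcomes reads: "Analyses of changes in secondary outcomes (physical activity, habit, wellbeing, physical health, functioning) will be run". Sedentary behaviour is not in it. The habit analysis relates changes in automaticity, including automaticity of sedentary behaviour, to one behaviour only: "and changes in physical activity within each group".

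**The concern.** A pilot of this size estimates a standard deviation well and a treatment effect poorly. The sample size is justified by the first, but the analysis section uses the second. Informing a larger trial is a declared purpose of this study, so a sizing rule that turns chance variation into a sample size weakens one of its main products. The next trial could be badly underpowered, or much larger than it needs to be.

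The choice of measure adds to this. Self-report is open to reporting that differs by arm: only the intervention group keeps daily tick sheets, and only for that group is the 4-week call also an occasion for motivational support (Intervention section). The posture-based measurement of the behaviour to be displaced is collected on everyone at the same time points, yet it plays no part in the sizing sentence.

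**Working it through.** The protocol gives no formula, error rate, power, effect size or standard deviation for the 120, so there is no figure to reproduce. The check is how precisely 120 participants estimate each candidate input.

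**Inputs from the protocol.** 120 participants (Study setting); 1:1 allocation (Randomization), hence at most 60 per arm; between-group changes over the first 8 weeks compared by *t* tests (Analysis of secondary outcomes). I therefore read the effect size as a standardised between-group difference in change, *d*. The protocol does not define it.

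**Assumed, not in the protocol.** True *d* = 0.30; dropout of 0%, 20% or 30%, leaving 60, 48 or 42 per arm; two-sided 5% level; 90% power.

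**Step 1: precision of the effect.** SE(*d*) = √(2/*n* + *d*²/(4*n*)).

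- *n* = 60: √(0.03333 + 0.09/240) = 0.184, and 1.96 × 0.184 = 0.36.
- *n* = 48: √(0.04167 + 0.09/192) = 0.205, and 1.96 × 0.205 = 0.40.

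**Step 2: what that does to the sample size.** *n* per arm = 2(1.960 + 1.282)²/*d*². For *d* = 0.30 this is 234; for *d* = 0.70 it is 43.

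| Completers per arm | SE of *d* | 95% range around 0.30 | *n* per arm implied at the upper end |
|---|---|---|---|
| 60 | 0.184 | -0.06 to 0.66 | 49 |
| 48 | 0.205 | -0.10 to 0.70 | 43 |
| 42 | 0.219 | -0.13 to 0.73 | 40 |

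In every row the lower end is negative, so the formula yields no usable sample size there.

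**Step 3: precision of the standard deviation.** The chi-square interval on 2*n* - 2 degrees of freedom gives these 95% limits as multiples of the estimate: 0.887 to 1.146 (60 per arm), 0.875 to 1.167 (48) and 0.868 to 1.18 (42). For a fixed target difference, sample size varies with the square of the standard deviation. With 48 per arm the multipliers are 0.875² = 0.766 and 1.167² = 1.362. A planned 234 per arm would correspond to a requirement between 234 × 0.766 = 179 and 234 × 1.362 = 319.

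**Step 4: consequence for the next trial.** In a simulation with true *d* = 0.30 and 60 per arm, the next trial was sized at 80% power from each observed *d* above 0.1. The cut-off is an assumption that keeps sample sizes finite. About 14% of estimates fell at or below it. Of the trials that were sized, 58% had true power below 80%, 28% had true power below 50%, and median power was about 72%. Some scatter around 80% is unavoidable, so the 28% is the more telling figure.

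**Step 5: the measure.** Steps 1 to 4 would apply equally to an effect size observed on activPAL data, so changing the measure alone would not cure the problem. The measure is a separate matter. Behaviour measures credits the device with telling sedentary behaviour apart from inactivity, and the Discussion makes progression depend on promise in both sitting and physical activity, but the sizing sentence uses self-reported activity alone.

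**The case against.** The strongest reply has four parts.

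- **The sizing sentence is not exclusive.** It says the effect sizes will inform the calculation, and Study setting mentions variability. That is fair, but no other input is named wherever the calculation is described.
- **Physical activity is a legitimate target.** The Abstract gives the booklet two aims, and the Endnote argues that sitting less necessarily means more activity. This stands. A reader might infer that the trial would be sized on the wrong behaviour; the documents do not support that. They support only that sitting, a declared target measured objectively, is left out of the sizing.
- **Sitting is not ignored in the analysis.** Behaviour measures commits total sitting time to analysis, Table 1 schedules it, and the Discussion describes the habit analysis in terms of behaviour generally. A reader might infer that sitting will never be analysed or related to habit; that goes too far. What remains is an inconsistency between the outcome list and the measures section, and a habit correlation worded more narrowly than its stated aim.
- **Reporting bias is a possibility only.** A reader might picture participants coached to report more activity to an unblinded researcher. Study procedure has questionnaires completed in participants' own time over a week, Study design describes participants as blinded to condition, and controls also receive activity recommendations. The remaining concern is the difference between arms in tick sheets and support.

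A reader might also infer that a low pilot estimate would cancel the definitive trial. The analysis section has no such rule.

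**Conclusion.** The point holds for the sizing sentence and should be fixed. An effect observed in at most 60 per arm carries a 95% interval of about ±0.36 standard deviations. Under the illustrative assumptions (true *d* 0.30, 48 completers per arm, 90% power), the sample size could come out near 43 per arm where 234 are needed, or not be calculable at all. The standard deviation is known to within about -12% to +17%, assuming roughly normal data. The true effect, dropout and power are my assumptions. The conclusion does not depend on the particular dropout rate, since the range is already wide with none.

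The omission of sitting from the outcome list and from the habit correlation is a lesser matter of consistency. Neither issue affects the primary outcomes of recruitment and attrition or the data to be collected, so it is not a bar to starting. No corrected sample size can be given, because the protocol states neither a standard deviation nor a target difference for sitting time.

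**What to change.** Reword the last part of the quantitative analysis under Analysis of secondary outcomes along these lines: *The sample size for the definitive trial will use the pilot's standard deviation of activPAL total sitting time, reported with its confidence interval, the correlation between baseline and follow-up, and the attrition rate. The target difference will be set on importance and not on the effect observed in the pilot. Self-reported physical activity will be supportive.*

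For consistency with Table 1 and Behaviour measures, add sedentary behaviour to the list of analysed outcomes. Correlate change in sedentary-behaviour automaticity with change in sitting as well as with change in physical activity.

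The cost is mostly wording: the activPAL data are already to be collected and recruitment had not begun. Two decisions are needed. The team must state a minimum important difference in sitting time. It must also say how sleep is handled, because the device is worn day and night and Table 1 lists no sleep or wake record; if waking sitting time is wanted, a derivation rule has to be written down.
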